## Baseline Assessments

Baseline assessments will include the completion of a standardized questionnaire (Appendix D: Study Standardized Questionnaire) followed by an appointment for a blood test to be taken by trained study staff. At this appointment we will take 4ml of blood for serological testing and 4ml of EDTA blood for storage and future research.

We have amended the online survey to include details about other emerging SARS-CoV-2 risk factors including medical conditions, ethinic background (BAME), home occupancy and ability to distance in the workplace. We have also added a second email address box that allows to follow up staff once they have left the trust, we have expanded the previous testing history to include additional information about home testing kits and other ELISA tests. Severe disease markers and complications of COVID-19 are also included and vaccination history is also included to prepare for when vaccination is rolled out.

Questionnaire development will utilise technology similar to other NHS staff surveys that allow completion on personal mobile devices. The questionnaire interface would be separated from the database, so they can employ different levels and methods of security. Many hosting services have built-in defences like firewalls, access logs, and authorisation protocols to restrict access, and the stored data should also be encrypted using a strong algorithm. Any data transferred to the database, e.g. via the interface, should also be encrypted to ensure that it is unreadable to anyone who intercepts it. If the database is a SQL database, the interface must also employ defences against "SQL injection" attacks, to prevent any code entered into forms doing any damage or exposing the data.
Regularly migrating identifiable information to internal servers (perhaps while leaving some anonymised statistical data if this is required) would also significantly reduce the risk of data theft.

## Subsequent Visits

Subsequent follow-up visits will be explained to all potential study participants as part of the informed consent process. The 2100 seropositive serology cohort will be followed intensively every 1 to 2 months for repeated serological testing whilst the 4900 seronegative comparison group will be followed 6 monthly. Participants from the positive arm of the study (as well as negative controls) will have the option of providing a 20ml in EDTA sample for T-cell assay studies and tissue typing, and a salivary sample for IgA analysis, both for research purposes. As these extra assays are research tests, results will not be provided to particpants. They will be formally consented for this.

After the initial intensive phase, all ~7000 recruits will be followed 6 monthly for the 6 year duration of the study. Follow-up visits will be arranged following the baseline assessment. The same blood tests 4ml EDTA and 4ml serum will be taken at each follow up appointment as well as the same symptom questionnaire. If a COVID-19 vaccination becomes available during the study we will undertake performance evaluation of an ELISA suitable for monitoring antibody titres to the vaccine target. We will then continue to follow up our cohort with the additional focus on the antibody titres to vaccination, duration of immunity following vaccination and the attack rate in the vaccinated and unvaccinated groups (with the previso that we expect the vaccine will have wide and rapid uptake).

Further detailed questionnaires will be sent to subgroups found to have higher incidence of infection, to further delineate the susceptibility and exposure factors.

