Within this initial planned cohort (**Study Flow Diagram 1, page 18**), a subset of ~400 staff members with confirmed symptomatic, PCR positive, antibody positive or equivocal, SARS-CoV-2 disease (and an additional 2100 staff sero-positive or equivocal staff members who were either PCR negative or asymptomatic) will be followed with intensive 1 to 2 monthly blood sampling to determine antibody titres to the SARS-CoV-2 specific protein using the *EDI^TM^* ELISA assay. Participants who are seropositive or equivocal will also have the option of providing an additional one off 20ml sample for T-cell assay analysis and a salivary sample for IgA analysis.

All 7000 recruited healthcare workers (2100 SARS-CoV-2 sero-positives and N~4900 seronegatives) will have blood taken for serological testing at baseline then at 6-monthly intervals for a total of 6 years. In addition to repeated serological testing, participants will continue as all healthcare workers at GOSH to have access to the staff testing program. This program tests symptomatic staff members by nasal swab PCR testing for SARS-CoV-2. Staff who have been tested for SARS-CoV-2 through the staff testing program will be consented for the PCR and serology results to be used in the study. All participants will also be asked to complete a detailed health and demographic questionnaire prior to each appointment, electronically. The technology design of the questionnaire will optimise participation. If key questions are missed, participants will be contacted by phone, text or email to optimise data collection and statistical analysis. As key factors impacting COVID-19 evolve, questions on review questionnaires will address these.

The data will enable us to determine the attack rate (percentage of healthcare workers with PCR proven infections/re-infections) and incidence (the rate of occurrence of disease) of SARS-CoV-2 infection amongst healthcare workers with and without antibodies. The comparison of the attack rate will indicate the protection antibodies provide. Further, the stratification of results by antibody titres, will provide information on whether a specific level of antibody confers protection.

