# Statistics

## Statistical methods to be employed (plan of analysis)

Antibody titres are expected to follow a negative exponential (log-linear) decay over time as seen following other respiratory viral infections. Serial antibody titres will be log-transformed and then multivariate linear regression models will be used to determine the predictors of antibody decay. Variable attack-rate between groups will be compared with a two-sample test of proportions and the incidence of COVID-19 disease between study groups will be compared using survival analysis with log-rank testing.

Fig.1: An estimated sample size of 4500-8000 total participants (with seropositive sample size of 1500-2700 participants, Fig.1, x-axis) provides 80% power at alpha 0.05 to detect an effect size of ≥17% decline in antibody titres over 12-months. This is based on a seropositivity prevalence of 33%, as observed in preliminary results so far and a negative exponential (log-linear) model of waning antibody titres, with 3 co-variate predictors of antibody decay, including sex, age and ethnicity (green line) or 4 co-variate predictors, including sex, age, ethnicity and co-morbidities (blue line). For comparison, the model was repeated based on 20% decline in baseline antibody titres over 12-months (using alpha 0.05), with the same 3 (orange line) or 4 (red line) co-variate predictors of antibody decline.

[figure not shown]

In order to determine the study power for varying effect sizes with unequal group sizes we undertook a two-sample power calculation of proportions with group sizes of 2100 seropositive cases and 4900 seronegative comparators using R (foundation for statistical computing) pwr function pwr.2p2n.test (Figure 2).

Figure 2. Power curve for group sizes of 2100 and 4900 participants showing that this study will have the power to detect an effect size of 0.07 i.e. a difference in the proportion in the attack rate between the two groups of 7%.

[figure not shown]

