We will also undertake an exploratory analysis using survival analysis to compare the hazards of infection in both groups over the course of the study using the date of reported and PCR proven SARS-CoV-2 infection as an event and the last follow up date or the final interview as the censorship date. We anticipate a high retainment rate in the study for three reasons a) GOSH has high baseline staff retention rates b) hospital staff already understand the rationale and the importance of this research and c) we have already received high levels of interest and engagement with the study.

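### The vaccinated v unvaccinated comparison uses attack rate, a percentage of people, although vaccination starts during follow-up, so the figure mixes vaccine protection with time spent in each state

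*Protocol*

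**What the plan says.** Secondary objective 9 (Objective and purpose) is to review antibody responses to vaccination and the infection rates that follow. It names no denominator.

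The measure is named under Subsequent Visits. The paragraph is conditional, opening "If a COVID-19 vaccination becomes available during the study", and among the added aims it lists "the attack rate in the vaccinated and unvaccinated groups (with the previso that we expect the vaccine will have wide and rapid uptake".

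Description of study design gives two separate measures: "attack rate (percentage of healthcare workers with PCR proven infections/re-infections) and incidence (the rate of occurrence of disease". The first is a share of people, the second a rate. They are introduced for staff with and without antibodies.

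The statistics section (plan of analysis) assigns one method to each measure. For the first: "Variable attack-rate between groups will be compared with a two-sample test of proportions". For the second: "the incidence of COVID-19 disease between study groups will be compared using survival analysis with log-rank testing". An exploratory survival analysis will "compare the hazards of infection in both groups over the course of the study"; this follows the power text for 2100 seropositive and 4900 seronegative staff.

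Baseline Assessments says of the questionnaire that "vaccination history is also included to prepare for when vaccination is rolled out". No section treats vaccination as a state that changes over time, splits follow-up at the dose, or censors there.

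**The concern.** A percentage of people compares two groups fairly only if membership is fixed and both are observed for about the same time. Neither holds here. No vaccine existed at enrolment, so every vaccinated participant first contributes unvaccinated time. The protocol itself expects most staff to move across quickly. The two states can therefore last very different lengths of time within six years, and the state that lasts longer collects more infections whatever the vaccine does.

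At stake is the infection part of secondary objective 9. The estimate would depend on when the vaccine arrived and how staff were classified, as well as on protection. Correcting the comparison by baseline serostatus would not correct this one, because the vaccination groups form during follow-up.

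**Working it through.** The protocol gives no sample size, event count or effect for this comparison, so there is no figure of its own to reproduce. Its Figure 2 concerns serostatus.

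**Inputs**
- Follow-up: 6 years = 72 months (Subsequent Visits).
- Assumed, not in the protocol: constant infection hazard h of 0.2, 0.5 or 1% per month; vaccination of all vaccinees at month T = 8, 12, 18 or 24; true hazard reduction 0 or 80%.

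**Rule A: infections split by status when they occurred**, each state's percentage taken among those uninfected on entering it.
- Unvaccinated: 1 − exp(−hT).
- Vaccinated: 1 − exp(−k·h·(72 − T)), with k = 1 (no effect) or 0.2 (80% effective).
- Example, h = 1%, T = 12, no effect: 1 − exp(−0.12) = 11.3% v 1 − exp(−0.60) = 45.1%; ratio 4.0.
- Same, 80% effective: 0.2 × 60 = 12 months' equivalent exposure, so 11.3% v 11.3%; ratio 1.0.

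| T (months) | Ratio, no effect (true hazard ratio 1) | Ratio, 80% effective (true hazard ratio 0.2) |
|---|---|---|
| 8 | 6.2 to 7.6 | about 1.6 |
| 12 | 4.0 to 4.8 | 1.0 |
| 18 | 2.5 to 2.9 | about 0.6 |
| 24 | 1.8 to 1.9 | 0.41 to 0.43 |

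Ranges run over the three hazards.

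**Rule B: ever v never vaccinated, whole follow-up, 80% effective.**
- Ever: 1 − exp(−hT − 0.2h(72 − T)). Never: 1 − exp(−72h).
- Example, h = 1%, T = 12: 1 − exp(−0.24) = 21.3% v 1 − exp(−0.72) = 51.3%; apparent efficacy 1 − 0.416 = 58%.
- Over all T and h: 44 to 70%.

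**Rule C: counting starts at a roll-out at which all vaccinees are vaccinated at once.**
- Both groups are observed for 72 − T months. With no effect the ratio is exactly 1.
- With 80% efficacy, 1 − [1 − exp(−0.2h(72 − T))] / [1 − exp(−h(72 − T))] gives 75 to 79%. The small shortfall arises because a risk ratio over a long period is not a hazard ratio.
- Now assume an average delay of 3 months from roll-out to dose, 60 months remaining and h = 0.5%. Ever/never grouping gives 1 − exp(−0.015 − 0.057) = 6.9% v 1 − exp(−0.30) = 25.9%, an apparent efficacy of 73%, against 77.5% without delay. Splitting by status at infection gives 5.5% over 57 months v 1.5% over 3 months, ratio 3.7. How much bias returns again depends on the rule.

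**A second model** (90% uptake at year 1, hazard 0.05 per year, six years, never-vaccinated staff kept as unvaccinated throughout) gives Rule A ratios of 3.17 for no effect (22.1% v 7.0%) and 0.70 for 80% efficacy. If people are instead classed by status at infection or at the end of follow-up, a useless vaccine looks protective: 22.1% v 48.5%, ratio 0.46.

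**Person-time under the same assumptions.** For h = 1%, T = 12:
- Unvaccinated: 0.1131 infections over 0.1131/0.01 = 11.31 person-months, rate 0.010.
- Vaccinated, no effect: 0.4512 over 45.12, rate 0.010; ratio 1.
- Vaccinated, 80% effective: 0.1131 over 0.1131/0.002 = 56.5, rate 0.002; ratio 0.2.

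The true ratio is recovered without reference to T.

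**The case against.** The strongest reply is that the vaccine comparison appears in a visit-schedule section, is conditional, and fixes no grouping rule, time origin or test. The attack-rate definition and the power calculation were written for serostatus. The sentence that gives the two-proportion test also gives a log-rank test for incidence. If it covers vaccine groups, a time-based analysis is planned beside the percentage; if it does not, the two-proportion test is not prescribed for them either. Objective 9 speaks of rates after vaccination, which suggests counting from roll-out or dose, where Rule C shows little bias.

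Much of this stands. The protocol nowhere ties the two-proportion test to vaccination by name; the tie comes from its general rule for attack rates. The grouping rule could properly be set in a statistical analysis plan, which is not at hand.

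Two things survive. The protocol does name attack rate for this contrast and defines it apart from incidence, so the choice of measure has been made and is not merely left open. And an ordinary log-rank test on ever/never vaccinated would not repair it, because time before the dose would be credited to the vaccinated group.

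A reader might go further and infer that the result would show only duration, that an effective vaccine would necessarily look useless or harmful, or that a false result would come with a small p-value. The documents do not support this. The figure mixes duration with protection. Apparent harm arises under Rule A only with early roll-out; later roll-out and ever/never grouping show protection. At a ratio of 1.0 the test would not give a small p-value.

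**Conclusion.** The point holds in a limited form. The stated measure ignores unequal and changing time at risk in a comparison where most participants are expected to change state. That follows from the protocol's wording and needs no assumed figure.

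Size and even direction rest on assumptions: constant hazard, roll-out time, uptake, and above all a classification rule the protocol does not state. The range runs from almost no bias (prompt, simultaneous roll-out with counting from that date) to a no-effect ratio of 1.8 to 7.6 when infections are split by status at infection. Changes in infection pressure over calendar time were not modelled; they are a further reason not to compare early unvaccinated with late vaccinated months. The comparison serves one of nine secondary objectives and carries no power claim, so this should be corrected but does not touch the primary objective.

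**What to change.** For objective 9, replace the attack-rate percentage and two-proportion test with infections per person-time, or with Cox regression in which vaccination is a time-dependent exposure: each person counts as unvaccinated until the dose date and as vaccinated afterwards. Use calendar date as the time scale, so that the two states are compared within the same epidemic period. Amend the sentence under Subsequent Visits to match; objective 9 can stay as worded.

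The cost is a change of wording plus one check. Vaccination history is already collected, but the questionnaire is not shown, so confirm that it records dose dates. The drawback should be stated in the plan: information comes only from calendar periods in which vaccinated and unvaccinated staff coexist, and with rapid uptake these will be short and precision limited.

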# Objective and purpose

| **Objectives** | **Outcome Measures/Endpoints** |
| --- | --- |
| **Primary Objective** | To determine the kinetics (rate of change) of SARS-CoV-2 specific protein antibody titres in proven cases of SARS-CoV-2 over the 6 month period following infection. |
| **Secondary Objectives** | 1. To determine the proportion of completely asymptomatic healthcare workers who have evidence of SARS-CoV-2 antibodies in their serum indicative of past infection 2. To determine the attack rate of SARS-CoV-2 in healthcare workers who have antibodies versus those who do not have antibodies 3. To determine the immune correlates of protection (antibody titres sufficient for protection) against future exposure to SARS-CoV-2 4. To investigate the roles of T-cell function and IgA in those with seropositivity to SARS-CoV-2. 5. To examine key risk factors influencing susceptibility to SARS-CoV-2. These include social determinants of health, such as housing, work and transport in the urban setting. 6. To ascertain clinical manifestations of COVID-19 disease and long term consequences of disease. 7. To pool international data in standardized form across hospital sites for longitudinal comparative review of risk factors and health service impact. 8. To assess the impact of COVID-19 on health worker staffing in hospitals and inform strategies for future planning. 9. To review antibody responses to vaccination against SARS-CoV-2 following it’s availability and analyse subsequent infection rates. |

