# Data Management

## Source Documents

The study will not require access to any of the participants medical records as part of this research. Instead new recruits will be asked to help complete an online questionnaire about their health, symptoms and exposure to SARS-CoV-2. Systems already employed by Occupational Health at GOSH have been duplicated to allow data collection of on online questionnaires on GOSH secure servers. This process has an established system of governance approved by GOSH ICT department. No hard copies of the identifiable data will be downloaded. The laboratory data will be stored as for existing occupational health medical information (such as Hepatitis B serology) which are stored on a secure NHS trust laboratory server. Samples will be stored in -70C freezers with a laboratory number unliked from any patient identifiers. Only named study staff will have access to the data. On all study-specific documents, other than the signed consent, the participant will be referred to by the study participant number/code, not by name.

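### The further detailed questionnaires have no lower-incidence comparison group, so factors recorded only there cannot be contrasted between higher- and lower-incidence staff

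*Protocol*

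**What the plan says.** Section 9.5 of the Protocol (Subsequent Visits) closes with a rule for extra data collection: "Further detailed questionnaires will be sent to subgroups found to have higher incidence of infection, to further delineate the susceptibility and exposure factors". It names no other recipients. It also does not say how a subgroup is defined or how much higher its incidence must be.

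The rule serves the fifth secondary objective in section 6 (Objective and purpose): "To examine key risk factors influencing susceptibility to SARS-CoV-2".

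The further questionnaires come on top of routine ones that are not limited to subgroups:

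- Section 7.1 (Description of study design): "All participants will also be asked to complete a detailed health and demographic questionnaire prior to each appointment, electronically". The same section adds: "As key factors impacting COVID-19 evolve, questions on review questionnaires will address these".
- Section 9.4 (Baseline Assessments): "We have amended the online survey to include details about other emerging SARS-CoV-2 risk factors including medical conditions, ethinic background (BAME), home occupancy". Ability to distance at work is also covered.
- Section 13.1 (Source Documents): "new recruits will be asked to help complete an online questionnaire about their health, symptoms and exposure to SARS-CoV-2".
- Appendix B schedules demographics and medical history at follow-up for both cases and the comparison group.

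Section 9.5 describes the repeated form more narrowly, since the follow-up blood tests are to be taken "as well as the same symptom questionnaire". The questionnaire itself is not in the text available for this review, so how much exposure detail everyone is asked for again at follow-up cannot be confirmed.

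**The concern.** The extra questionnaires are triggered by the question of why certain subgroups have more infection than others. Answering it needs the same items from the others. If most staff in a high-incidence subgroup report some exposure, that proportion means little unless its frequency elsewhere is known.

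Selecting subgroups on the outcome adds a second difficulty. With several subgroups, some will rank high by chance. Without a concurrent comparison group, nothing in the extra answers would show that such a subgroup's exposures are ordinary.

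This is a rule about which data are collected. An analysis plan written later can choose a method, but it cannot recover answers that nobody was asked for. What is at stake is the new information that the further questionnaires are meant to add to the risk-factor objective.

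**Working it through.** No figure in the Protocol depends on this rule, so there is none to reproduce. The check has a textual part and two illustrations on assumed inputs.

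**1. Which contrasts exist under the rule as written**

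| Items | Asked of | Higher- v lower-incidence subgroups | Infected v uninfected within a selected subgroup |
|---|---|---|---|
| Routine (sections 7.1, 9.4, 13.1) | all participants | available | available |
| Further detailed (section 9.5) | higher-incidence subgroups | not available | available if exposure varies |

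**2. How far the within-subgroup contrast can substitute**

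From the Protocol: about 7,000 participants. Assumed: a high-incidence subgroup of 1,000 and 6,000 others; infection risk 10% if exposed and 5% if not (risk ratio, RR, of 2); exposure prevalence 20% among the others; exposure prevalence e inside the subgroup varied from 50% to 100%.

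With E exposed and U unexposed staff,

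SE(log RR) = √[0.90/(0.10·E) + 0.95/(0.05·U)].

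Power is for the two-sided 5% test of two proportions, with pooled variance under the null and unpooled under the alternative.

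Worked case, e = 95%, subgroup only: E = 950, U = 50. SE = √(0.90/95 + 0.95/2.5) = √(0.0095 + 0.3800) = 0.62. For power, the pooled risk is 97.5/1,000 = 0.0975 and the null SE is √[0.0975 × 0.9025 × (1/950 + 1/50)] = 0.0430. The alternative SE is √(0.09/950 + 0.0475/50) = 0.0323. Then (0.05 − 1.96 × 0.0430)/0.0323 = −1.06, which gives 14%.

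For the same e with all 6,000 others also asked: E = 950 + 1,200 = 2,150 and U = 50 + 4,800 = 4,850, so SE = √(0.90/215 + 0.95/242.5) = 0.09. With a random sample of 1,000 of the others (200 exposed, 800 not): E = 1,150 and U = 850, so SE = √(0.90/115 + 0.95/42.5) = 0.17.

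| Exposed inside subgroup | Subgroup only: SE, power | Plus 1,000 others: SE, power | Plus all 6,000: SE, power |
|---|---|---|---|
| 50% | 0.24, 85% | 0.17, 98% | 0.09, >99.9% |
| 80% | 0.33, 62% | 0.17, 99% | 0.09, >99.9% |
| 90% | 0.45, 33% | 0.17, 99% | 0.09, >99.9% |
| 95% | 0.62, 14% | 0.17, 99% | 0.09, >99.9% |
| 100% | not estimable | 0.18, 99% | 0.09, >99.9% |

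The last two columns pool subgroup and others without adjustment, so they assume that exposure is the only reason the risks differ. Among the 6,000 others alone, which avoids that assumption, SE = √(0.90/120 + 0.95/240) = 0.11. Among the sample of 1,000 alone, SE = √(0.90/20 + 0.95/40) = 0.26 and power is 72%.

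**3. Selection by chance**

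Assumed: 7,000 staff in equal subgroups, all with the same true risk of 5%, and the three highest selected. With 20 subgroups of 350, the standard deviation (SD) of an observed rate is √(0.05 × 0.95/350) = 1.165%. The three largest of 20 standard normal values average about 1.47, so the selected subgroups would show 5% + 1.47 × 1.165% = 6.7% on average with nothing to explain. The figure depends on the assumed division:

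- 10 subgroups of 700: 5% + 1.06 × 0.824% = 5.9%.
- 40 subgroups of 175: 5% + 1.81 × 1.648% = 8.0%.

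The Protocol specifies neither the subgroups nor a top-three trigger, so these figures show the mechanism only.

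**The case against.** The strongest case on the other side is that section 9.5 describes a supplementary second step. A subgroup can be found to have higher incidence only by comparing it with the rest, and that first comparison uses questionnaires completed by everyone. Those cover medical conditions, ethnic background, home occupancy, distancing at work and exposure, and they are to be updated as new factors emerge. Nothing in section 9.5 forbids a comparison group, no planned test depends on these answers, and a chance trigger costs only some extra electronic forms.

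Most of this stands, and it rules out three stronger readings that a reader might infer:

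- That follow-up exposure data come only from high-incidence subgroups. The text does not say so; the further questionnaires are additional to routine ones given to all.
- That the risk-factor objective has no comparator. For routine items it has the full cohort.
- That risk factors cannot be estimated at all from the further questionnaires. Any selected subgroup still contains uninfected staff. In the illustration, RR 2 is detected with 85% power when half of a subgroup of 1,000 is exposed.

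The objection does not cover items asked only in the further questionnaires. Those forms are useful because they ask more than the routine ones, so the gap falls on the new information. The within-subgroup contrast is also weakest when an exposure is nearly universal there, which is a situation that could itself explain a high incidence. Nor can the sampling be left to a later analysis plan, because who is asked is settled when the forms go out.

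**Conclusion.** The concern holds in a limited form. Followed as written, section 9.5 collects the further items from subgroups chosen for higher observed incidence and plans no lower-incidence comparison group. Factors captured only there cannot be contrasted between higher- and lower-incidence subgroups, the within-subgroup contrast fades as exposure approaches 100%, and chance-high subgroups would not be recognised as such.

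The absence of a comparison group is read directly from the text. The sizes are illustrative: every input except the total of about 7,000 is assumed. Severity is minor. The point affects one of nine secondary objectives and leaves the primary objective, the sample size and the planned tests untouched. One uncertainty remains: if the routine follow-up form already repeats detailed exposure items for everyone, the gap is smaller still.

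**What to change.** Add one sentence to section 9.5: whenever a further questionnaire is sent to a higher-incidence subgroup, the same items go at the same time to a random sample of participants from the other subgroups, or to all participants, and infected staff are compared with uninfected staff across both. Sending the forms at the same time keeps the recall period alike in both groups. If no comparison group is wanted, state instead that results from these questionnaires are descriptive and will not be used to explain differences between subgroups.

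The cost is small. Questionnaires are already electronic, so the change adds a modest burden on more participants and no visits or samples. In the illustration, a sample of 1,000 other staff already brings the standard error at 95% exposure from 0.62 to 0.17, so asking everyone is not essential.
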